| Secondary
a) Efficacy of Atorvastatin in avoiding electric, morphological and biomarkers deterioration;

b) safety of Atorvastatin treatment   | a) Deterioration from baseline of
i) arrhythmia burden (PVC, non-sustained and sustained VA, VF, appropriate ICD shocks); ii) other morphological parameters (ventricular volumes, function, both at ECHO and CMR); iii) ECG parameters; iv) blood parameters;

b) monitoring of AE and patient's well-being. | a)
i) Deterioration from baseline of the frequency of premature ventricular contractions, non-sustained and sustained ventricular arrhythmias, episodes of ventricular fibrillation, appropriate defibrillator shocks (measured by Holter, defibrillator and loop recorder interrogation at T18).
ii) Variation from baseline of morphological parameters, such as ventricular volumes (ml), parietal thicknesses (mm), fibrotic replacement characteristics (mm  ), cardiac functional parameters as ejection fraction (%) or Fractional shortening (%), heart movements (number and extension of bulging and wall motion abnormalities) measured at ECHO and CMR at T18.
iii) Variation from baseline of the electrocardiogram parameters (ms or voltage) at T18.
iv) Variation from baseline of biomarkers at T18 (concentrations, Units).
b)
i) Number and severity of adverse events (blood safety parameters variation and number and severity of patient-reported adverse effects) till T18.
ii) Variation in the score of the psychological questionnaires at T18 respect to baseline. |

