#### Medical Conditions

- Known hypersensitivity to atorvastatin or any of the excipients
- Moderate or severe liver disease (persistent elevation of transaminases more than 3 times the upper limit of the normal laboratory reference range)
- Muscle disease (CK levels significantly elevated more than 3 times the upper limit of the normal laboratory reference range)
- Left ventricular ejection fraction  $< 35\%$
- Congestive heart failure defined by the New York Heart Association (NYHA) as class III or IV.
- Known cardiomyopathy of other origin: post ischemic, hypertrophic, idiopathic dilated, restrictive; known moderate-to-severe mitral or aortic valvulopathy; pulmonary hypertension; congenital cardiac abnormalities
- Hypercholesterolemic patients that, according to guidelines [4], require the use of lipid lowering drugs.

- Heart transplantation
- Estimated life expectancy of less than 2 years
- Any other medical condition that, in the judgment of the investigator, places the patient at risk or makes the patient unreliable or limits the patient's ability to complete the study

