#### **Follow-up Phone call, end of the study (19th month +/- 1 month)**

This visit includes:

- Patient-reported outcome collection
- AE review
- SAE review

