#### **8.5. Safety Assessments**

Planned time points for all safety assessments are provided in the SoA.

The most common (about 1:100) atorvastatin-related adverse reactions, based on data from clinical trials and extensive post-marketing experience are: allergic reactions, hyperglycemia, headache, pharyngolaryngeal pain, epistaxis, constipation, flatulence, dyspepsia, nausea, diarrhea, myalgia, arthralgia, pain in extremities, muscle spasms, joint swelling, back pain, abnormalities of liver function tests, increased creatine kinase, increased serum transaminases.

Uncommon (less than 1:100) adverse reactions include: loss of appetite, male gain, decreases in blood sugar levels, insomnia, dizziness, numbness or tingling in the fingers and toes, reductions of sensation to pain or touch, change in sense of taste, loss of memory, blurred vision, ringing in the ears and/or head, vomiting, belching, abdominal pain upper and lower, inflammations in pancreas or liver, skin rash and itching, hair loss, neck pain, muscle fatigue, chest pain, swelling especially in the ankles, raised temperature, urine tests that are positive for white blood cells.

Rare (1:1,000) adverse reactions include: serious allergic reaction, severe skin peeling, swelling or rash, Muscle weakness, pain, associated to red-brown discoloration of urine and high temperature (suggestive of rhabdomyolysis), visual disturbance, unexpected bleeding or bruising cholestasis (yellowing of the skin and whites of the eyes), tendon injury.

Very rare (1:10,000) adverse reactions include: Lupus-like disease syndrome (including rash, joint disorders and effects on blood cells); unexpected or unusual bleeding or bruising, suggestive of a liver complaint, hearing loss, gynecomastia.

The parameters used to ensure safety are mainly constituted by blood tests and patient reported adverse events.

Enrolled patients will be encouraged to report adverse events spontaneously even without direct questioning by the investigator. For each adverse event reported by the patient, the investigator will obtain all information and documentation necessary for an accurate description of the adverse event.

The adverse events can be reported by the patient at any time, as soon as possible during-after occurrence. Blood tests at the visits T2, T4, T9 and T18 might uncover some hidden adverse events.

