#### **9.1.3 Analysis of safety variables**

AEs will be presented in terms of the number of AE, the incidence, severity and relationship to the study drug, overall and by body system and preferred term. SAEs will be presented in the same way.

Results for routine laboratory tests will be assessed as being below the lower limit of the normal range, within the normal range or above the upper limit of the normal range. The frequency of patients reporting an abnormal or abnormal clinically significant laboratory value at screening and follow-up will be presented for each laboratory variable. Vital signs will be presented using descriptive statistics.

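### The laboratory safety summary in Protocol 9.1.3 does not show how large CK and transaminase rises are, and does not say which on-treatment draws it covers

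*Protocol*

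**What the plan says.** Section 4 (Objectives and Endpoints, secondary b) defines the safety measure up to T18 as "Number and severity of adverse events (blood safety parameters variation" together with patient-reported effects.

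Section 9.1.3 sets out how laboratory results are summarised. Each result falls below the lower limit of normal, "within the normal range or above the upper limit of the normal range". A second sentence adds: "The frequency of patients reporting an abnormal or abnormal clinically significant laboratory value at screening and follow-up will be presented for each laboratory variable".

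Entry criteria (Section 6.2, Medical Conditions) exclude "CK levels significantly elevated more than 3 times the upper limit of the normal laboratory reference range" and, for the liver, "persistent elevation of transaminases more than 3 times the upper limit of the normal laboratory reference range". Patients between 1 and 3 times ULN can therefore be enrolled.

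The Schedule of Activities puts hepatic and muscle bloods at screening, T2, T4, T9 and T18, and Section 8.5 gives the purpose: "Blood tests at the visits T2, T4, T9 and T18 might uncover some hidden adverse events". The month-19 contact is headed "Follow-up Phone call, end of the study" and lists no blood test.

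**The concern.** Section 9.1.3 does more than stay silent on laboratory grading: it states a scale. A three-level position relative to the normal range cannot express severity, which Section 4 promises. The one added refinement, a count of clinically significant values, has no size threshold and so depends on each investigator's judgement.

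The time axis is also loose. Four on-treatment draws are scheduled, and the summary names only follow-up.

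At stake is a secondary objective, the safety of 80 mg atorvastatin in this population. Section 8.5 lists raised creatine kinase, raised transaminases and abnormal liver function tests among the most common reactions. If the few large elevations are pooled with every marginal excursion above ULN, the reader of the report cannot see whether the arms differ in elevations of any consequence.

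**Working it through.** The protocol gives no figure on this point to reproduce. The check applies the stated scale to example values and then asks whether other parts of the protocol supply what it omits.

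**1. The scale applied to examples.** Inputs: the three categories of 9.1.3, and the 3 x ULN entry limit of 6.2, which allows baselines up to 3. The values are chosen for illustration, in multiples of ULN. Rule: up to 1 (and not below the lower limit) is within; more than 1 is above.

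| Baseline | On treatment | Reads as | Above 3 x ULN? | Above 10 x ULN? |
|---|---|---|---|---|
| 0.6 | 1.2 | within to above | no | no |
| 0.6 | 3.5 | within to above | yes | no |
| 0.6 | 12 | within to above | yes | yes |
| 1.5 | 1.5 | above to above | no | no |
| 1.5 | 3.5 | above to above | yes | no |
| 2.5 | 2.6 | above to above | no | no |
| 2.5 | 12 | above to above | yes | yes |

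The first three rows share one reading and the last four share another. Size is lost from a normal baseline as well as a raised one.

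**2. How many patients this concerns.** Section 9.1 plans 51 per arm. Section 8.5 puts the most common reactions, including raised CK and transaminases, at about 1 in 100. Section 3.3 defines common as 1/100 up to 1/10. Neither gives the size of the rise, so the range of rates p below is an assumption. Expected number = 51p; chance of at least one = 1 - (1 - p)^51.

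- p = 0.01: 51 x 0.01 = 0.51 expected; 1 - 0.99^51 = 0.40
- p = 0.02: 1.02 expected; 1 - 0.98^51 = 0.64
- p = 0.05: 2.55 expected; 1 - 0.95^51 = 0.93
- p = 0.10: 5.1 expected; 1 - 0.90^51 = 0.995

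The relevant cases would number from about none to five per arm. Such small counts are informative only if kept apart from mild excursions.

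**3. Whether other outputs show the size.**

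- *Adverse event tables.* Sections 8.3.1.1, 8.3.1.3 and 8.5.4 make new or worsening laboratory abnormalities adverse events, entered when the investigator judges them clinically relevant. Section 8.3.2.3 grades severity by interference with usual function, so a symptom-free rise of any size fits Grade 1.
- *Biomarker outcome.* CK, AST/ALT, ALP and bilirubin are in the list in 8.5.6, and Section 4 measures biomarker change from baseline at T18. T2 and T4, the dedicated safety checks, are outside that outcome.
- *General comparison of changes.* Section 9.3 compares changes in variables of interest at different time points by t test or rank test. It does not name these analytes, and a comparison of averages or ranks does not count patients with large rises.
- *Listings.* Section 9.3 lists all CRF data by patient and centre. Peak values are there, but not compared by arm.

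**The case against.** The strongest reply is that 9.1.3 is one display within a wider safety analysis. The same paragraph counts clinically significant values. A patient who enters with a raised CK and worsens has an adverse event by 8.3.1.3, tabulated with severity and relationship. Reasons for and dates of definitive treatment discontinuation are recorded (8.2.1), and every value is listed. All of this stands. A reader might infer that large rises would be hidden; the protocol does not support that. What the reply leaves open is a comparison of size between arms, as the check above shows.

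A reader might also take follow-up to mean the T19 call, or a single late time point that loses a transient T2 or T4 rise. The text does not say so. T19 has no blood draw, and Section 9.1.4 speaks of a planned follow-up visit in a general sense, so all post-screening draws is a reasonable reading. What stands is only that the draws are not named.

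Nor is the 3 x ULN entry limit the cause, since the same loss occurs from a normal baseline. Section 8.5.4 does set aside findings tied to the underlying disease, but restores those more severe than expected; nothing suggests that large CK or liver rises would be attributed to the cardiomyopathy.

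Finally, cut-points and shift tables often belong in a statistical analysis plan, and a separate one may exist. That lowers the weight of the point. It does not remove it, because Section 9.3 says the plan is described in this section, and 9.1.3 states a scale that does not fit the outcome in Section 4.

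**Conclusion.** The point holds as a minor-to-moderate reporting weakness. The summary stated in 9.1.3 cannot distinguish a trivial CK or transaminase rise from a large one at any baseline, does not define clinical significance by size, and does not identify the on-treatment draws it covers. The remaining routes make large rises visible case by case, but give no by-arm comparison of their size.

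The conclusion rests on the stated categories and needs no assumed event rate. The 1% to 10% range only indicates scale, and the 3 x and 10 x ULN marks in the examples are illustrative. The protocol gives no basis for claiming that any particular imbalance between arms would be missed. The primary endpoint, the error rate and data collection are unaffected.

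**What to change.** In 9.1.3, for CK, AST/ALT, ALP and bilirubin, replace or supplement the three-level summary with a table of each patient's worst post-baseline value over T2, T4, T9, T18 and any unscheduled draw. Express it as a multiple of the local laboratory's ULN, for example up to 1, >1-3, >3-5, >5-10 and >10. Cross-tabulate it with the screening category, by arm, in the Safety population. These are reporting bands and change no clinical rule. In the same section, name the draws that follow-up covers and state how clinically significant is decided.

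Cost: reference limits for each local laboratory must be held in the eCRF, since 8.5.6 has these tests done at the different centres, and a few more tables must be produced. No extra blood, visits or patients are needed.

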#### **9.1.4 Missing data**

All reasonable efforts will be made to reduce the rate of missing data, since any method used for imputation for missing observations would be based on untestable assumptions.

In case of impossibility of performing CMR in some patients, the patients will be excluded from the analysis of the specific elements, based on CMR, of the secondary endpoint. The same parameters acquired by ECHO will be used.

Investigators will be trained about the importance of patient retention and full data capture. Also, any reasonable attempts should be made by the Investigators to emphasize continued patient's participation for the full duration of the trial. However, in order to minimize missing data, if a patient cannot refer to the site for a planned follow-up visit, the Investigator will try to obtain any relevant

information from the patients, including documents/laboratory results available from local medical care.

However, if a patient is lost at follow-up after the T9 data collection visit, imputation of missing data may be implemented, when possible, followed by sensitivity analyses.

If the patient drops-out before T9 the patient will be simply excluded from the analysis.

We expect that a larger number of patients will abandon the study if they are in the Atorvastatin group, respect to the Placebo one, since they have probability to experience atorvastatin-related adverse effects. The 15% drop-out rate described in the sample size calculations, takes into account this possibility.

An effort will be made to understand the reasons of drop-outs, mainly to assess whether they are related to the outcomes (ACM-linked events). In this case, to avoid a possible bias (the most serious patients abandon the study) a post-hoc statistical correction may be implemented.

We will try to reduce unused data (collected data items that will not directly link to a result and will therefore not be counted in the final manuscript), and spurious data or spurious inferences, to improve study performance, lower time and costs of collection and storage, and address ethical concerns.

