### 3.3. Benefit/Risk Assessment

If the hypothesis proves to be correct, we expect to slowing down disease progression, both from the tissue and the electrical points of view, and consequently an improvement in symptoms and a reduction in arrhythmic risk.

The proposed therapy is expected to bring significant clinical benefit compared to existing therapies in Arrhythmogenic Cardiomyopathy context, none of which targets the fibro-adipogenic disease progression. The use of statins in patients suffering from ACM may have beneficial effects in reducing the progression of the pathology and avoiding the most severe consequences of the disease. Indeed, beyond the described canonical lipid-lowering effects, atorvastatin has known pleiotropic effects, as anti-oxidant, anti-inflammatory and anti-arrhythmic, leading, in ACM patients, to lowering of the triggering factor oxLDL, reduction of the inflammatory mediated disease bursts, and moderation of the arrhythmia burden.

The expected results will be beneficial for the health system, reducing costs and efforts for the management of ACM patients.

In addition, the patient in the study will be guaranteed close follow-up and more in-depth care than during routine visits.

However, it is possible that a subgroup of patients taking Atorvastatin may experience side effects.

In the database of placebo-controlled atorvastatin clinical trials involving 16,066 patients (8755 Atorvastatin vs. 7311 placebo) treated for an average period of 53 weeks, 5.2 per cent of patients on atorvastatin discontinued the trial due to adverse reactions, compared to 4.0 per cent of placebo-treated patients.

Below is the profile of atorvastatin adverse reactions based on data from clinical studies and extensive post-marketing experience. The frequencies of the estimated reactions are classified according to the following convention: common ( $\geq 1/100$ ,  $< 1/10$ ); uncommon ( $\geq 1/1,000$ ,  $< 1/100$ ); rare ( $\geq 1/10,000$ ,  $< 1/1,000$ ); very rare ( $< 1/10,000$ ); frequency unknown (cannot be defined based on available data).

Infections and infestations

Common: nasopharyngitis.

Haemolymphopoietic system disorders

Rare: thrombocytopenia

Immune system disorders

Common: allergic reactions

Very rare: anaphylaxis

Metabolism and nutrition disorders

Common: hyperglycaemia

Uncommon: hypoglycaemia, weight gain, anorexia

Psychiatric disorders

Uncommon: nightmares, insomnia

Nervous system disorders

Common: headache

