### **8.2.3. Withdrawal from the Study**

Patients will be informed that they have the right to withdraw from the study at any time (withdrawal of consent), without prejudice to their medical care, and are not obliged to state their reasons. Patients who have withdrawn consent to the study or who for any cause have discontinued the study cannot be reincluded in it. Investigators may decide to discontinue the study for a patient for any clinical problem, or if other issues arise (such as, for example, non-compliance with the Protocol, etc.).

The withdrawal or discontinuation of the patient from the Study must be documented in the CRF. If a patient fails to return to the centre for a scheduled visit, attempts should be made to contact the patient to ensure that the reason for not returning is not a SAE. Likewise, if a patient declares his/her wish to discontinue from the study e.g. for personal reasons, an attempt should be made to establish that the true reason is not a SAE (bearing in mind the patient is not obliged to state his/her reasons).

Safety laboratory tests should be performed whenever possible at patient withdrawal.

It is also possible for the study to be terminated prematurely by the Sponsor in case of:

- new information leading to an unfavorable risk-benefit assessment of the IMP, such as occurrence of previously unknown significant adverse reactions or unexpectedly high intensity or incidence of known adverse reactions, or other unfavorable safety findings;
- Trial no longer justified for clinical or ethical reasons;
- withdrawal of IMP from the market for safety reasons.
- Finally, the trial could be terminated or suspended at the request of health authorities.

If the study will suffer of more than the expected 15% of dropout, the endpoints will be calculated anyway, as a proof of principle. In case of missing data to achieve the aims, these will be imputed using multiple imputation and a sensitivity analysis will be performed on the imputed data.

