#### **8.3.7.1. Emergency procedures**

The blinding should only be broken for valid medical or safety reasons, e.g., in case of a serious adverse event for which there is a reasonable possibility of a relatedness with the study medication (i.e., serious adverse reaction) and it is necessary for the PI or another delegated site staff member to know which treatment the patient is receiving before he/she can be properly treated for the event.

If the code is broken for an urgent safety situation, the patient will be withdrawn from the study.

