### 9.2. Populations for Analyses

The Safety population will consist of all patients who received any study medication and will be based on the treatment actually received. The Safety population will be used to present the demographic and baseline data, and all safety data.

The Intent to Treat (ITT) population will consist of all patients who are randomized and receive the IMP (either Atorvastatin or placebo); it will be based on the treatment randomized, regardless of the treatment actually received. The ITT population will be used to present efficacy data.

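### Excluding patients who drop out before T9 contradicts the ITT efficacy set, does not fit the multiple-imputation text, and leaves the primary comparison open to bias of unknown size and direction

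*Protocol*

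**What the plan says.** Three sections of the protocol bear on who enters the primary analysis and how gaps are handled.

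- **Section 9.2 (Populations for Analyses)** defines the ITT set as patients randomised and given IMP, analysed as randomised, and adds: "The ITT population will be used to present efficacy data".
- **Section 9.1.4 (Missing data)** splits losses at T9. Before T9: "If the patient drops-out before T9 the patient will be simply excluded from the analysis". After T9: "imputation of missing data may be implemented, when possible, followed by sensitivity analyses".
- **Section 8.2.3 (Withdrawal from the Study)** says: "In case of missing data to achieve the aims, these will be imputed using multiple imputation", followed by a sensitivity analysis. It draws no line at T9.

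Section 9.1.4 also forecasts unequal loss: "We expect that a larger number of patients will abandon the study if they are in the Atorvastatin group", because of drug-related adverse effects. It notes separately that bias could arise if the most serious patients leave, and says a post-hoc correction may then be made. No method is named.

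Two further places affect how much data is lost. Section 8.3.7.1 says: "If the code is broken for an urgent safety situation, the patient will be withdrawn from the study". Section 8.2.1 refers to the Schedule of Activities for the data to be collected when treatment is discontinued, but the Schedule has no column for that event.

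**The concern.** An analyst cannot keep every dosed patient in the efficacy set and also remove those lost before T9. Nor can the analyst impute missing data generally while deleting the same patients.

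The conflict matters because of where the cut-off falls. The T2 and T4 visits, with liver and muscle blood tests, come before T9, so early intolerance is likely to be found in the window where drop-out means exclusion. Removal after randomisation that may depend on arm, and perhaps on disease severity, weakens the protection that randomisation gives. The 15% allowance in section 9.1 replaces numbers; it does not restore comparability.

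The rule concerns the primary endpoint, and changing it after unblinding would not be credible.

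**Working it through.** **The plan's own figures.** Section 9.1 gives a difference of 2.4 points, SD 4.5, one-sided alpha 0.05 and power 80%.

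- n per arm = 2 × (4.5/2.4)² × (1.645 + 0.842)² ≈ 43.5, so 44 per arm and 88 in total. This reproduces. The exact t calculation gives 79.9% power at 44 per arm.
- 88 × 1.15 = 101.2, hence the stated 102. Dividing by 0.85 gives 104, a trivial difference.

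**Precision.** Counting all of the 15% drop-out as excluded, one-sided power for 2.4 points is:

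| Excluded, atorvastatin v placebo | Analysed | Power |
|---|---|---|
| 15% v 15% | 43 v 43 | 79.0% |
| 20% v 10% | 41 v 46 | 79.3% |
| 25% v 5% | 38 v 48 | 78.6% |

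The exclusion hardly touches power. The issue is validity.

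**Bias formula.** Let d be the share of an arm excluded and g the extra T18 decline that excluded patients would have shown compared with retained ones. Retained patients then look better than the whole arm by d × g. With A for atorvastatin and P for placebo, the error in the estimated benefit is

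bias = dA × gA − dP × gP,

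and a positive value favours atorvastatin. If g is the same in both arms, bias = (dA − dP) × g.

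**Inputs.** The protocol gives no drop-out split for this trial and no outcome for leavers. Its only per-arm figures are in section 3.3: "5.2 per cent of patients on atorvastatin discontinued the trial due to adverse reactions, compared to 4.0 per cent of placebo-treated patients". They come from other placebo-controlled trials averaging 53 weeks and count adverse reactions only. The other loss rates below are assumptions. So is g, set at 0.5 to 1 SD (2.25 to 4.5 points) and equal in both arms.

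| Loss before T9, atorvastatin v placebo | dA − dP | Bias at g = 2.25 | Bias at g = 4.5 | Share of 2.4 |
|---|---|---|---|---|
| 5.2% v 4.0% | 0.012 | 0.03 | 0.05 | 1–2% |
| 10% v 5% | 0.05 | 0.11 | 0.23 | 5–9% |
| 15% v 5% | 0.10 | 0.23 | 0.45 | 9–19% |

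**Sensitivity to the equal-g assumption.**

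- g = 0 in both arms: bias is 0 whatever the loss rates.
- Only atorvastatin leavers differ, losing the full 2.4-point benefit, with 5.2% excluded: 0.052 × 2.4 = 0.12 points in favour of atorvastatin.
- Only placebo leavers do worse, by 4.5 points, with 5% excluded on placebo: −0.05 × 4.5 = −0.23 points, against atorvastatin.

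**Error rate, upper-end case.** Assume no true effect, 20% v 10% excluded (every drop-out counted as excluded), and leavers worse by 2.4 or 4.5 points in both arms. The bias is 0.24 or 0.45 points, and the nominal 5% one-sided error becomes 8.1% or 11.8%.

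**The case against.** The strongest defence is that unequal drop-out alone does not bias anything. The protocol attributes the expected imbalance to adverse effects and nowhere says that early atorvastatin leavers would have had worse strain. Its remark about the sickest patients is conditional and not tied to an arm. Its only per-arm rates imply a very small bias. Even 0.45 points is under half the standard error of the comparison, 4.5 × √(2/44) = 0.96. All of this stands. A reader might infer that the result will be biased in favour of atorvastatin; the document does not support that.

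Other stronger readings also fail:

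- **A completers' analysis.** Patients lost after T9 may be imputed, so only those lost before any post-baseline ECHO are removed.
- **Three competing missing-data rules.** Section 9.2 defines a population. Sections 8.2.3 and 9.1.4 are the two missing-data texts, and they can partly be read together: one names the method, the other limits it to patients with T9 data. The sentence in 8.2.3 also follows one about drop-out above 15% and could be taken as limited to that case. Neither reading reconciles the exclusion with section 9.2.
- **Stopping IMP or any code break ends follow-up.** Section 8.2.1 does not say that patients who stop IMP leave the study, and the T9 and T18 ECHO are not restricted to patients on treatment. The missing Schedule column is a documentation gap. Section 8.3.7.1 withdraws patients only after a code break in an urgent safety situation.

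A separate SAP might settle the point, but section 9.3 says the analysis plan is described in the protocol itself. The exclusion is a stated rule, not a detail left open.

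**Conclusion.** Wrong as written. The pre-T9 exclusion contradicts the ITT efficacy set in section 9.2 and does not fit the imputation text in section 8.2.3. That conclusion rests on the wording alone and is firm.

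The consequence is less certain. The primary comparison is open to bias, because the protocol forecasts unequal loss and recognises possible severity-related loss without a pre-specified answer. Under an equal excess decline of 2.25 to 4.5 points, the bias runs from about 0.03 to 0.05 points with the protocol's external rates up to 0.45 points (19% of the design effect) at an assumed 15% v 5%. It is zero if leavers would not have differed, and its sign can reverse if the excess decline differs by arm.

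**What to change.** 1. Delete the exclusion sentence in section 9.1.4. State one rule, worded alike in sections 8.2.3, 9.2 and 9.1.4, that keeps all ITT patients in the primary analysis under a single pre-specified missing-data method.
2. Replace the optional post-hoc correction with a pre-stated delta-adjusted or placebo-based sensitivity analysis. This is needed because T9 is the first post-baseline ECHO: patients lost earlier have only a T0 strain, and a repeated-measures model or missing-at-random imputation adds little for them.
3. State that the T9 and T18 ECHO already in the Schedule are sought from every randomised patient who has not withdrawn consent, whether or not still taking IMP.
4. Reconcile section 8.2.1 (its reference to a Schedule entry that does not exist) and section 8.3.7.1 (withdrawal after an urgent code break) with the ITT set. How patients are managed clinically in those situations is for the sponsor to decide.

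The cost is a few sentences of protocol text, slightly more analysis work, and some visits by patients no longer on treatment. Those visits are already scheduled.
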